## Abstract

**Background:**

The sole presence of deep submucosal invasion is shown to be associated with a limited risk of lymph node metastasis. This justifies a local excision of suspected deep submucosal invasive colon carcinomas (T1 CCs) as a first step treatment strategy. Recently Colonoscopy-Assisted Laparoscopic Wedge Resection (CAL-WR) has been shown to be able to resect pT1 CRCs with a high R0 resection rate, but the long term outcomes are lacking. The aim of this study is to evaluate the safety, effectiveness and long-term oncological outcomes of CAL-WR as primary treatment for patients with suspected superficial and also deeply-invasive T1 CCs.

**Methods:**

In this prospective multicenter clinical trial, patients with a macroscopic and/or histologically suspected T1 CCs will receive CAL-WR as primary treatment in order to prevent unnecessary major surgery for low-risk T1 CCs. To make a CAL-WR technically feasible, the tumor may not include > 50% of the circumference and has to be localized at least 25 cm proximal from the anus. Also, there should be sufficient distance to the ileocecal valve to place a linear stapler. Before inclusion, all eligible patients will be assessed by an expert panel to confirm suspicion of T1 CC, estimate invasion depth and subsequent advise which local resection techniques are possible for removal of the lesion. The primary outcome of this study is the proportion of patients with pT1 CC that is curatively treated with CAL-WR only and in whom thus organ-preservation could be achieved. Secondary outcomes are 1) CAL-WR’s technical success and R0 resection rate for T1 CC, 2) procedure-related morbidity and mortality, 3) 5-year overall and disease free survival, 4) 3-year metastasis free survival, 5) procedure-related costs and 6) impact on quality of life. A sample size of 143 patients was calculated.

**Discussion:**

CAL-WR is a full-thickness local resection technique that could also be effective in removing pT1 colon cancer. With the lack of current endoscopic local resection techniques for > 15 mm pT1 CCs with deep submucosal invasion, CAL-WR could fill the gap between endoscopy and major oncologic surgery. The present study is the first to provide insight in the long-term oncological outcomes of CAL-WR.

**Trial registration:**

CCMO register (ToetsingOnline), NL81497.075.22, protocol version 2.3 (October 2022).

## Background

A segmental colon resection with lymph node dissection is associated with significant morbidity (24%) and mortality (2%) [1], regardless of T-stage. In T1 colorectal cancer (CRC), three independent histological features have been identified to be risk factors for lymph node metastases (LNM), i.e. (lympho-) vascular invasion, poor (high-grade) differentiation (G3) and high-grade tumor budding (Bd2-Bd3) [2–7]. A completely removed (R0) T1 CRC can be classified as low risk T1 when histological examination shows none of the high risk factors for LNM. Prior retrospective studies report a very low risk of LNM (1%) for low risk T1 CRC [8–11]. As this negligible risk does not outweigh the significant morbidity and mortality of an segmental resection, patients with low risk T1 CRC are sufficiently treated with a local resection.

As upfront risk stratification is not possible, all patients with suspected T1 CRC could receive initial local treatment according to current national guidelines. An additional segmental resection with lymph node dissection is only indicated if histological examination shows high risk factors for LNM or when an incomplete local resection (R1) is performed. It has been proven that secondary surgery after initial local endoscopic resection (or an attempt) has no negative effects on the development of LNM or cancer recurrence [8, 12–16]. Therefore a primary local en-bloc resection strategy in order to prevent unnecessary upfront major surgery for low risk T1 CC patients is justified. Moreover, patients who underwent local endoscopic therapy have similar quality of life (QoL) without increased fear of cancer recurrence compared to patients who underwent a segmental resection [17].

In contrast to previous insights, the presence of deep invasion is no longer recognized as high risk factor for LNM. A suspected deeply-invasive T1 colon carcinoma (CC) is therefore not a strong indicator for a segmental resection [18]. Unfortunately, the therapeutic options to perform a ‘’full thickness’’ local resection in the colon are scarce. The R0-resection rate and safety of an endoscopic submucosal dissection (ESD) in the colon is significantly compromised in case of deeply invasive lesions and therefore not recommended in these cases [19, 20]. This means that the endoscopic Full Thickness Resection (eFTR) is currently the only available technique to remove deeply-invasive T1 colon carcinomas (CC) up to 15 mm [21].

Recently, we have shown that Colonoscopy-Assisted Laparoscopic Wedge Resection (CAL-WR) is an effective and safe technique to remove endoscopically unresectable benign colonic lesions (LIMERIC-trial [22]). The technical success rate of CAL-WR was 93% and a R0-resection was achieved in 91% of the patients with low morbidity (6%) and no mortality. Subsequently, CAL-WR was introduced as a feasible ‘’full-thickness’’ resection technique for the removal of suspected T1 CCs [23], however long-term oncological outcomes of CAL-WR are yet unclear. In particular for large deep-invasive lesions, CAL-WR could fill the gap between the current endoscopic resection techniques and major oncologic surgery, providing more patients an minimal invasive organ-preserving treatment option.

The aim of this study is to prospectively register the effectiveness, safety, and costs of CAL-WR as primary treatment of suspected (deep-invasive) T1 CC and to provide insight in its long-term oncological outcomes.

## Methods

In this prospective multicenter clinical trial, patients with suspected T1 CC (after assessment by an expert panel) will receive CAL-WR as initial treatment in order to prevent unnecessary segmental resections for low risk T1 CC.

### Study population

*In order to be eligible for inclusion, patients must meet the following inclusion criteria:*
Non-pedunculated lesion which is macroscopically suspected for (deep-invasive) T1 colon carcinoma during endoscopy (Hiroshima C1-3 [24]) and/or histologically proven adenocarcinomaSize < 40 mm (endoscopic assessment)Localized at least > 25 cm proximal from the anus (measured endoscopically)Localized with sufficient distance to the ileocecal valve to place the linear stapler > 18 years old

*A potential subject who meets any of the following criteria will be excluded from participation in this study:*
Rectal carcinomaDistant metastasis at baseline > 50% circumferential growth of the lesionPrior local endoscopic resection or attempt (lifting not included)History of malignancy in the past 5 years or current presence of another malignancy

### Objectives

The primary objective of this study is to determine the proportion of patients with pT1 CC for whom CAL-WR was shown to be formerly a curative treatment (i.e. low-risk T1 CC, R0) and in whom an (additional) segmental resection could thus be prevented. Secondary objectives are to evaluate CAL-WR’s technical success and R0 resection rate for T1 CC, procedure-related morbidity and mortality, the 5-year overall and disease free survival, 3-year metastases free survival, its costs, and the impact on QoL.

### Study design

This study is a prospective multicenter clinical trial in The Netherlands. Patients with a macroscopic suspected and/or histological suspected T1 CC, meeting the in-and exclusion criteria, are eligible for inclusion. Based upon endoscopic images, the expert panel decide whether a lesion is suspect for a T1 CC. To reduce subjectivity and standardize the assessment, all expert panel members will use internationally applied scoring systems; Paris classification [25], Hiroshima classification [24] and report the morphological malignant features that are present. In particular the presence of a demarcated area with neoplastic pit pattern (Hiroshima C1-3) will weigh heavy when a lesion is screened for eligibility by the expert panel [26]. Depending on the macroscopic assessment and estimated depth of invasion, the expert panel will state if the lesion is suspected for T1 CC (superficial or deeply-invasive) and subsequently recommend which local resection strategie(s) (ESD, eFTR or CAL-WR) is/are suitable.

According to the recommendation of the current national Dutch colorectal carcinoma guideline, all suspected T1 CCs must be discussed in the local multidisciplinary team meeting to determine the best treatment strategy. If CAL-WR is regarded to be a suitable treatment by all parties, technically possible and preferred by the patient, inclusion of the patient will follow (Fig. 1). All eligible patients rejected for inclusion by the expert panel will be registered in a screening-log. Preoperative measurement of CEA (carcinoembryonic antigen) is required. In accordance with the current Dutch T1 CRC guideline, tumor staging through imaging of the chest and abdomen is not recommended in case of suspected T1 CRCs and therefore not indicated before the procedure. Written informed consent will be obtained and the patient and procedure related items will be registered in a web-based database (ResearchManager, Version 6.5). The estimated duration of inclusion will be 24 months and the total follow-up period of each patient is 5 year.

**Fig. 1 Fig1:**
[figure not shown]
Flowchart patient enrollment. Legend: ESD—Endoscopic submucosal dissection, eFTR—Endoscopic full-thickness resection, CAL-WR—Colonoscopic-Assisted Laparoscopic Wedge Resection

### Quality assurance

#### Expert panel

Patients with an macroscopic and/or histologically suspected T1 colon carcinoma, meeting the inclusion criteria, will be submitted to a multidisciplinary expert panel to evaluate each case for eligibility. This panel will consist of two surgeons and five gastroenterologists. The gastroenterologists, who are specialized in endoscopic removal of tumors by ESD/eFTR and work in different participating hospitals, will assess the chance of malignancy using international standardized scoring systems [24, 25, 27]. Subsequently, all experts report which local resection methods are possible in the particular case (eFTR/ESD/CAL-WR). Inclusion is only possible when at least three gastroenterologists of the expert panel conclude that the lesion is suspected for T1 CC and eligible for removal through CAL-WR, and when one of the surgeons considers a CAL-WR technically feasible. For thorough evaluation, endoscopic images of the tumor will be sent including overview and close up images and with use of advanced imaging techniques such as narrow band imaging. To minimalize inclusion of T2 colon carcinomas, all gastroenterologist in the expert panel will be trained to distinguish deep invasive submucosal (T1) from muscularis propria (T2) colorectal cancer, by use of the recently developed scoring system by Koyama et al. [28]. All individual reports of the expert panel members will be archived in the study database. (Paris classification, Hiroshima classification, morphological malignant features that are present, morphological features suspected for T2 CC, their individual conclusion (benign, suspected T1 CC or suspected for ≥ T2) and recommendation for treatment).

#### Participating surgeons

All participating surgeons must be experienced in laparoscopic colorectal surgery. Aiming to further standardize the procedure, all participating surgeons must have attended an e-learning concerning the technique and the possible pitfalls of the technique. However, the majority of the surgeons is already familiar with CAL-WR by participating in our previous trial [22]. Patients will be informed by the surgeon about the possibility of conversion into an laparoscopic or open major oncologic resection if perioperative CAL-WR is not feasible.

### CAL-WR technique

CAL-WR is a minimally invasive technique to locally resect lesions by using a linear stapler without making an anastomosis (Fig. 2). All included patients will undergo split-dose bowel preparation before the procedure. Patients are placed in French position under general anesthesia. The procedure is initiated with a diagnostic laparoscopy with the insertion of three trocars. At first, the spot in the colon is identified and the corresponding part of the colon will be mobilized. This is to ensure the ability to place the linear stapler, to make a CAL-WR possible. Secondly, the colonoscopy is performed. A suture is laparoscopically placed near the tumor with intraluminal endoscopic visualization. In case of a tumor close to the mesentery, the colonic wall can be dissected from the mesentery with preservation of the marginal artery. Traction is provided on the suture to enable positioning of the linear stapler. Before stapling off the tumor, patency of the colonic lumen (or the lumen of the ileum in case of a cecal lesion) as well as the total inclusion of the tumor is confirmed endoscopically. The resected specimen is then removed in an endobag through the 12 mm trocart. Lastly, the peritoneal surface as well as the luminal aspect of the colon is inspected for signs of bleeding or perforation before ending the procedure. Total operation time, used materials, and duration of endoscopy are reported in the online case report form.

**Fig. 2 Fig2:**
[figure not shown]
Colonoscopic-Assisted Laparoscopic Wedge Resection (CAL-WR) procedure

### Histopathological examination

Over the last years, a nation-wide cohort of pathologists with special interest in gastro-intestinal oncology were extensively trained to score the above and below mentioned histological risk factors, in the context of the PATCH-study (https://t1crc.com/research—KWF Dutch Cancer Society reference number: 12723 / 2019–2). To guarantee a high-quality histopathological assessment, all the resected specimen will be judged by PATCH-trained dedicated pathologist(s) of the participating centers.

The specimen will be processed through the following instructions (standard care). The pathologist receives the fresh resected specimen in toto, without manipulation of the staple line by the surgeon. The pathologist removes the staples, the lateral margins and deep peritoneal aspect will be inked with different colors. Thereafter, the specimen will be stretched on a paraffin block (or mesh), photographed, and fixed for 24 h at room temperature. After fixation, longitudinal sections of limited length and width of the whole specimen will be included and the specimen will be accessioned in toto. Histological diagnosis of the tumor is carried out in accordance with the current guidelines and will include histological type, invasion depth, tumor grade, presence of vascular/lymph invasion, grade of budding and margin status. Incomplete resection is defined as a resection margin of less than 0.1 mm (R1) [29] and/or when radicality cannot be determined (Rx). T1 CCs with the presence of one or more histological risk factors, i.e. (lympho-) vascular invasion, poor (high-grade) differentiation (G3) and high-grade tumor budding (Bd2-Bd3), are classified as high-risk T1 CC.

### Follow-up

After CAL-WR and subsequent histological examination, 3 groups will be formed i.e. (1) benign pathology, (2) low risk T1 CC (i.e. carcinomas with absence of histological high risk features for lymph node metastasis), and (3) high risk T1 CC (i.e. carcinomas with histological high risk features for lymph node metastasis) or accidentally found ≥ pT2 (Fig. 3). All patients diagnosed with a benign colonic polyp, will receive a follow-up colonoscopy after 1 year to evaluate local recurrence rate. Patients diagnosed with low risk T1 CC will undergo colonoscopy 12 and 48 months after curative radical (R0) resection, according to the current national guideline. In case patients are diagnosed with an incomplete resected low risk 1 CC, high risk T1 CC or ≥ pT2, completion surgery is advised. All patients with an indication for completion surgery will be staged with chest and abdomen imaging by computer tomography (CT) to rule out potential synchronous metastasis and will subsequently be discussed in the multidisciplinary team meeting. If completion surgery is considered to be beneficial, it needs to be performed within six weeks after initial CAL-WR in order to guarantee the patients’ oncological outcome [30]. In case of high complication risks and/or based on the patients’ choice, there can be refrained from a complementary resection and give preference to intensive follow-up. The impact of CAL-WR on QoL will be evaluated in all patients, also those that undergo completion surgery, using three questionnaires (EQ-5D-5L, QLQ CR29 and CWS). The questionnaires will be performed at baseline, at 3 and 36 months after the procedure. Participation in the national Prospectief Landelijk CRC cohort (PLCRC) is preferable for the questionnaires [31].

**Fig. 3 Fig3:**
[figure not shown]
Flowchart follow-up. Legend: CAL-WR—Colonoscopic-Assisted Laparoscopic Wedge Resection, Low risk pT1 – pT1 colon carcinoma without (lympho-) vascular invasion, poor (high-grade) differentiation and high-grade tumor budding, R0 – radical resection, R1 – irradical resection (resection margin of less than 0.1 mm), Rx—radicality could not be determined, High risk pT1—pT1 colon carcinoma with one or more of the following histological risk factors: (lympho-) vascular invasion, poor (high-grade) differentiation and high-grade tumor budding, CRC – colorectal cancer

### Outcomes

#### Primary endpoint

Proportion of patients with pT1 colon carcinoma for whom CAL-WR was shown to be a curative treatment (i.e. low-risk T1 CC, R0) and in whom an (additional) segmental resection could thus be prevented (percentage of patients).

#### Secondary endpoints

Effectiveness (technical success and macroscopic- and microscopic radical resection)30-day postoperative morbidity and mortality rate. Complications will be assessed according to the Clavien-Dindo classification. Clavien-Dindo grade I and II complications will be classified as minor and grade III-V complications as major.3-year metastasis free survival defined as the development of metastasis outside the area of the intended surgery (intensive surveillance), or after completion surgery.5-year overall survival and disease free survival (disease free survival is defined as the time between surgery until local cancer recurrence or detection of distant metastasis)Total procedure related and postoperative costs (‘in-hospital’ costs between the primary day of surgery until 30-days after discharge)Postoperative quality of life

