### Data analysis

Data on demographic and baseline characteristics will be summarized for continuous variables, in case of normal distribution by mean and standard deviation (SD), and in case of non-normal distribution by median and (interquartile) range. Discrete variables and categorical data will be presented as proportions of patients (percentages). All baseline characteristics and differences in secondary outcomes, such as morbidity and postoperative QoL, will be compared between patients that only received CAL-WR versus patients that received also additional oncologic resection, using the Student’s T-test (in case of normally-distributed continuous data) or the Mann–Whitney U test (in case of non-parametrical continuous data). Normality will be verified using the Kolmogorov–Smirnov test. A (two-sided) *p*-value < 0.05 will be considered significant. The primary endpoint will be described as the proportion (percentage with 95% confidence interval) of patients with pT1 CC where only local resection with CAL-WR appeared to be curative and thereby oncologic resection was prevented. The 5-year overall survival and disease free survival will be assessed using a Kaplan–Meier analysis*.* The 30-day postoperative morbidity and mortality will described as proportions (percentages). Data analysis will be performed by using the Statistical Program for the Social Sciences (SPSS) version 28.0 (IBM. Corp, Armonk, New York, USA).

The cost analysis will be conducted from a hospital’s perspective. Total procedure-related cost of CAL-WR will be calculated in Euro. Healthcare costs will be calculated by multiplying used healthcare services by the appropriated unit cost prices. Bottom-up micro costing will be applied. For all other healthcare services reference prices, will be used where available. Costs will be discounted to correct for inflation. Eventually, the cost efficiency of our strategy will be calculated, considering also the number of patients that will need two operations i.e. patients with high risk T1 or ≥ T2.

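### Disease-free survival is defined without death, so the Kaplan–Meier 5-year figure is a time to recurrence, and regional nodal recurrence is not clearly assigned to either listed event

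*Protocol article*

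**What the plan says.** The Secondary endpoints section lists 5-year overall survival and disease-free survival together and defines the latter: "disease free survival is defined as the time between surgery until local cancer recurrence or detection of distant metastasis". The events are local recurrence and distant metastasis; death from any cause is not among them. The Data analysis section then says "The 5-year overall survival and disease free survival will be assessed using a Kaplan–Meier analysis". It gives no rule for patients who die without recurrence, and no other section widens the definition. Under Study design, "the total follow-up period of each patient is 5 year".

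The neighbouring endpoint is worded as "3-year metastasis free survival defined as the development of metastasis outside the area of the intended surgery (intensive surveillance), or after completion surgery". It names neither death nor lymph nodes.

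On the role of the nodes, the Background says "An additional segmental resection with lymph node dissection is only indicated if histological examination shows high risk factors for LNM", an incomplete local resection being the other indication. It also reports "Prior retrospective studies report a very low risk of LNM (1%) for low risk T1 CRC". The Follow-up section allows that, for patients with an indication for completion surgery, "there can be refrained from a complementary resection and give preference to intensive follow-up".

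**The concern.** The label and the definition do not describe the same quantity. A reader takes disease-free survival to mean alive and free of disease. The definition measures only freedom from local or distant recurrence, and Kaplan–Meier treats a death without recurrence as if that patient could still recur later. A DFS that counts death cannot lie above overall survival; this one can.

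The article presents long-term oncological outcome as what the study will newly provide, and this endpoint is one of those meant to deliver it. Deaths that follow from the treatment strategy itself, such as a death after completion surgery, would not count as DFS events.

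The second strand is the lymph nodes. The strategy leaves them in place unless histology or margins indicate otherwise, and some patients with an indication may keep them. Yet the event list names only local and distant failure, so where a regional nodal recurrence belongs is left to the assessor.

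**Working it through.** **The plan's own figures.** The article states no DFS rate, event count or precision target, so there is no DFS figure to reproduce. Its only design figures concern the primary endpoint, and both reproduce: 1.96² × 0.45 × 0.55 / 0.1² = 95.08, rounded up to 96 pT1 patients; 96 / (0.75 × 0.90) = 142.2, rounded up to 143. Neither depends on how DFS is defined.

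**Effect of leaving out death.** Let r be the 5-year net risk of recurrence and d the 5-year net risk of death without recurrence. Constant, independent hazards are assumed.

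- Endpoint as written, deaths censored: 1 − r
- DFS with death as an event: (1 − r)(1 − d)
- Gap: d(1 − r)

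The article gives neither r nor d. The ranges below (r from 2 to 10%, d from 2 to 15%) are assumptions.

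| r | Endpoint as written | DFS counting death, d = 2 / 5 / 10 / 15% | Gap in points |
|---|---|---|---|
| 2% | 98.0% | 96.04 / 93.1 / 88.2 / 83.3% | 1.96 / 4.9 / 9.8 / 14.7 |
| 5% | 95.0% | 93.1 / 90.25 / 85.5 / 80.75% | 1.9 / 4.75 / 9.5 / 14.25 |
| 10% | 90.0% | 88.2 / 85.5 / 81.0 / 76.5% | 1.8 / 4.5 / 9.0 / 13.5 |

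The gap runs from 1.8 to 14.7 points. Its sign does not depend on the assumed values: it is positive whenever d is above zero.

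**Can it exceed overall survival?** If the death hazard is the same before and after recurrence, overall survival is 1 − d. With r = 5% and d = 10%, the endpoint as written is 95.0% and overall survival is 90.0%. Higher mortality after recurrence would lower overall survival further.

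**As a measure of recurrence.** Here the error goes the other way and is small. Cumulative incidence of recurrence with death competing is [ln(1 − r) / (ln(1 − r) + ln(1 − d))] × [1 − (1 − r)(1 − d)]. At r = 10% and d = 15% this is 0.393 × 0.235 = 9.24%, against 10% from one minus Kaplan–Meier. The overstatement is 0.8 points, the largest in the assumed ranges.

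**What the article's own rates give.** These are partial counts only.

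- Sample size section: 45% of 96 pT1 patients are assumed cured by local resection, so 0.55 × 96 = 52.8, about 53, are not. Background: 2% mortality for segmental resection. If all 53 had completion surgery, 53 × 0.02 = about 1.1 deaths, or 1.1 / 96 = about 1.1 points, would not be DFS events. Deaths from other causes come on top and are not given.
- Low-risk, completely resected patients: 0.45 × 96 = about 43. At the 1% nodal risk in the Background, 43 × 0.01 = about 0.4 patients. For high-risk patients who forgo completion surgery, the article gives neither a number nor a rate.

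**The case against.** DFS is one of several descriptive secondary endpoints. No hypothesis, comparator, threshold or power is attached to it, and the primary endpoint, sample size and mid-term check do not use it. Overall survival is reported beside it, so deaths are not hidden from the reader. All of this stands and limits the severity. It does not make the DFS label or estimate correct, and because the article states both the definition and the method, this is not a detail left to a fuller document.

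On the nodes, a reader might infer that the definition excludes regional nodal recurrence and so misses the failure that local resection risks. The text does not support that. Local cancer recurrence is undefined and could be read as locoregional. A node left behind after a wedge resection could also count under the 3-year metastasis endpoint, since the article itself speaks of lymph node metastasis. The contrary reading is also open: if the intended surgery is the segmental resection with node dissection, regional nodes lie inside its area and may fall under neither endpoint. What stands is an unassigned event, small by the article's figures in low-risk patients and unquantified in the rest.

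A reader might also infer that survival will be pooled with benign lesions, or that the figure will be compared with published DFS values. The article plans neither.

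**Conclusion.** The point holds for death: a stated definition, analysed by a stated method, yields a quantity that is not disease-free survival. Relative to a DFS counting death it is too high whenever anyone dies without recurrence. That direction follows from the definition alone.

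The size does not. About 2 to 15 points rests on the assumed 5-year ranges above and on constant, independent hazards. A reader might settle on a narrower and more striking figure: annual hazards of 0.5–1% for recurrence and 2–3% for death give gaps from e^(−0.05) − e^(−0.15) = 9.1 points to e^(−0.025) − e^(−0.175) = 13.6 points. The arithmetic is right, but the article supplies none of those rates, and the low end of the plausible range is much smaller.

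For nodal recurrence the finding is limited to an ambiguity that the wording should settle. Overall, this is a correction worth making to a descriptive secondary endpoint, and it does not threaten the trial's main result.

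**What to change.** Define DFS as the time from CAL-WR to the first of local recurrence, regional nodal recurrence, distant recurrence or death from any cause, and analyse it by Kaplan–Meier.

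If the recurrence-only measure is wanted, alone or in addition, call it time to recurrence, name regional nodal recurrence as an event, and report its cumulative incidence with death as a competing event.

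The cost is one definition and, if both measures are kept, one small extra analysis. Deaths and recurrences are already needed for the existing endpoints. The downside is a less favourable DFS figure. The change is best made before outcome data are examined.
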